**Methods and analysis:**

This assessor-blinded multicentre randomised controlled trial includes about 1000 participants with a first-ever stroke, of which 752 participants require secondary prevention based on their 24-hour movement behaviour. Participants will be randomly assigned to the experimental group (RISE intervention + usual care) or control (usual care) group. RISE is a 15-week blended care intervention: primary care physiotherapists coach people in their home setting using behaviour change techniques and the RISE eCoaching system. This system consists of: (1) an activity monitor, (2) a smartphone application that provides real-time feedback and contains e-learning modules and (3) a monitoring dashboard for the physiotherapist. A close relative of the participant is involved during the intervention to provide social support. The primary outcome is the effectiveness of the RISE intervention regarding the prevention of MACE measured at one year post randomisation using survival analysis comparing the experimental and control groups. Secondary outcomes include cost-effectiveness for MACE prevention and QALYs and changes in 24-hour movement behaviour over time using compositional data analysis.

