	Inclusion criteria: if people are aged ≥18 years, had a first-ever symptomatic stroke (excluding transient ischaemic attacks) within 6 months before inclusion, are able to walk independently (functional ambulant category ≥3), were independent regarding activities of daily living pre-stroke (Barthel Index >18), are not participating in a physical rehabilitation programme lasting ≥3 months and are discharged to the home-setting.
	Exclusion criteria: if people are unable to understand the Dutch language or have severe comorbidities that withhold them from safely reducing and interrupting their sedentary time
Study type	Interventional
	Allocation: assessor-blinded multicentre randomised controlled trial
Date of first enrolment	November 2023
Target sample size	1000
Recruitment status	Recruiting
Primary outcome(s)	Effectiveness of the RISE intervention regarding prevention of MACE measured at 1 year post randomisation comparing experimental and control groups.
Key secondary outcomes	Cost-effectiveness of the RISE intervention for MACE prevention and quality adjusted life years.Changes in 24-hour movement behaviour (sedentary behaviour, physical activity and sleep) over time between the experimental and control group.

MACE, new major cardiovascular event or death; N.A., not applicable; RISE, Reduce and Interrupt sedentary behaviour using a blended behavioural intervention to Empower people at risk towards sustainable 24-hour movement behaviour change.

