### Participants

Participants will be recruited via stroke units in about 30 hospitals in the Netherlands, the general practitioner (GP) clinic or open recruitment between November 2023 and December 2025. They will be approached post discharge in the hospital or via a GP’s letter and asked for permission to share their contact details with the researchers. Open recruitment will occur via articles and flyers, encouraging interested individuals to contact the researchers directly. With participants’ consent, their eligibility will be assessed by consulting the healthcare professional in charge. The number and reasons for non-participation will be recorded.

Participants will be eligible for participation if they are aged ≥18 years, had a first-ever symptomatic stroke (excluding transient ischaemic attacks (TIA)) within 6 months before inclusion, are able to walk independently (functional ambulant category ≥3), were independent regarding activities of daily living pre-stroke (Barthel Index>18), are not participating in a physical rehabilitation programme lasting ≥3 months and are discharged to the home-setting. Participants will be excluded when they are unable to understand and speak the Dutch language or have severe comorbidities that withhold them from safely reducing and interrupting their sedentary time.

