### Study procedures

After obtaining informed consent (online supplemental file 1), baseline measurement (T0) takes place at the participants’ home (figure 1). During this visit, an activity monitor will be provided to objectify the 24-hour movement behaviour. If participants require secondary prevention, it will be based on their 24-hour movement behaviour pattern^11^: *sedentary prolongers,* ≥9.5 hours of sedentary time per day, >50% of the sedentary time is spent in bouts >30 min and not reaching the physical activity guideline (150 min MVPA during the week); *sedentary movers,* <9.5 hours of sedentary time and (1) ≤50% of the sedentary time spent in bouts >30 min or (2) not reaching the physical activity guideline.^16 17^ Randomisation will take place for *sedentary prolongers* and *sedentary movers,* with stratification according to these two profiles. All other participants will be excluded after baseline measurement.

Concealment of allocation will be ensured by individual randomisation by an independent researcher. Randomisation to either the experimental or control group will be done using a computer-generated random sequence with block sizes of two, four and six (Castor Electronic Data Capture 2021, Ciwit B.V., Amsterdam, The Netherlands).

The experimental group receives the RISE intervention from a trained primary care physiotherapist for 15 weeks. Follow-up measurements take place at the end of the intervention period (T1) (ie, 4 months post randomisation) and at 6 months (T2), 9 months (T3) and 12 months post randomisation (T4) (figure 1). Due to the nature of the intervention, participants and primary care physiotherapists will not be blinded for treatment allocation. The researcher who performs the measurements at T1 is blinded to treatment allocation.

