### Sample size

The required number of subjects was calculated using the Lachin and Foulkes Logrank Test module in the PASS 2008 software (Hintze J. PASS 2008, Kayesville, Utah, USA www.ncss.com). The power calculation was performed based on detecting a difference in MACE between the experimental and control group. In line with the effectiveness of cardiac rehabilitation, we expect that the RISE intervention will decrease the number of MACE by 35%.^43^ In the control group, 25% is expected to have MACE in the first year.^3 44^ To not underpower the study, an event rate of 20% in the control group in the first year is used. Participants will enter the study during an accrual period of 1.5 years. Enrolment is assumed to be completed for 50% when 50% of the accrual time has passed. A follow-up period of 1 year is assumed to have a 20% loss to follow from the experimental group and a 20% loss to follow from the control group. A two-sided log rank test with a power of 0.85 and a 0.05 significance level to detect a difference of 0.07 between 0.80 and 0.87 (the proportions surviving the experimental and control group after 1 year) led to an overall sample size of 752 participants (of which 376 are in the experimental group and 376 in the control group).

*Sedentary prolongers* and *sedentary movers* will be the target population of the study and will be randomised to the intervention or control group. From our RISE cohort study, we know that 67% of the participants with stroke were *sedentary prolongers* or *sedentary movers*.^11^ Therefore, we expect around 1000 participants need to be screened during baseline measurement (figure 1). Based on our pilot study, we expect to include 2–3 participants per hospital per month. With 20 participating hospitals, this will lead to the expected number of 762 participants by December 2025.

Our secondary outcome, effectiveness of the RISE intervention on reducing SB, can be assessed in a smaller population. From the RISE pilot study, we know that the target group had an average of 11 hours and 21 min of sedentary time per day, with an SD of 77 min/day.^14^ This means, with a two-sided significance level of 0.05, a power of 80%, that a sample size of 47 people per group is needed to detect a minimal detectable change of 45 min in SB between our groups.^45^ Accounting for a dropout rate of 20%, 59 participants per group will be used for this analysis.

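### The 67% eligible share, 752 randomised and about 1000 screened cannot all hold: at 67%, 752 needs about 1,122 screened, and 1000 yields 670

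*Protocol article*

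**What the plan says.** In the protocol article, the Sample size section gives the log-rank calculation, which "led to an overall sample size of 752 participants", 376 per arm. It then turns to how many people must be assessed to find them. Citing the group's own cohort, it says "we know that 67% of the participants with stroke were" in one of the two profiles that will be randomised (sedentary prolongers or sedentary movers). From this it concludes: "Therefore, we expect around 1000 participants need to be screened during baseline measurement".

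The same pair of numbers appears elsewhere. The abstract says that the trial "includes about 1000 participants with a first-ever stroke, of which 752 participants require secondary prevention", and Table 1 lists "Target sample size 1000". Study procedures makes the profile a strict filter, since only the two profiles go on to randomisation: "All other participants will be excluded after baseline measurement".

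The Sample size section closes with a recruitment forecast based on 2 to 3 participants per hospital per month: "With 20 participating hospitals, this will lead to the expected number of 762 participants by December 2025". The Participants section refers to "stroke units in about 30 hospitals in the Netherlands", together with general practice and open recruitment.

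**The concern.** Three printed figures are presented as one chain of reasoning: the number needed, the share that qualifies, and the number to screen. The third is given as a consequence of the first two but cannot be obtained from them. The direction matters, because the stated screening number is too small for the stated share.

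The figure of 1000 is also the one shown to the outside world, as the target sample size in Table 1. Anyone who budgets baseline visits, or judges when recruitment is complete, from that number would be working towards a total that does not deliver the powered sample on the article's own eligibility rate. Table 1 gives the recruitment status as open, so the figure can still be corrected in time to be useful.

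**Working it through.** **Inputs, all from the protocol article**

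- Required number randomised: 752 (Sample size).
- Eligible share: 0.67 (Sample size).
- Expected number screened: about 1000 (Sample size, abstract, Table 1).
- No route to randomisation outside the two profiles (Study procedures).
- For power: one-year event-free proportions 0.80 and 0.87, two-sided 0.05, power 0.85, accrual 1.5 years at an even rate, follow-up 1 year, 20% loss per arm (Sample size).

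**Step 1: reproduce the 752.** The named method is Lachin and Foulkes. I take exponential hazards, uniform accrual over R = 1.5 years, total duration T = 2.5 years, and exponential loss of 20% per year.

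- Hazards: λ₁ = −ln 0.80 = 0.2231; λ₂ = −ln 0.87 = 0.1393; mean λ̄ = 0.1812; loss η = −ln 0.80 = 0.2231.
- Event probability: P(λ) = λ/(λ+η) × {1 − [e^(−(λ+η)(T−R)) − e^(−(λ+η)T)] / [(λ+η)R]}. This gives P(λ₁) = 0.267, P(λ₂) = 0.178, P(λ̄) = 0.224.
- With φ(λ) = λ²/P(λ): φ(λ₁) = 0.1867, φ(λ₂) = 0.1090, φ(λ̄) = 0.1467.
- N = [1.960 × √(4φ(λ̄)) + 1.036 × √(2φ(λ₁) + 2φ(λ₂))]² / (λ₁ − λ₂)² = [1.960 × 0.7659 + 1.036 × 0.7690]² / 0.0839² ≈ 751.

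The plan's 752 is therefore reproduced on its stated inputs and is not in question here.

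**Step 2: from randomised to screened.** Screened = randomised / share.

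- 752 / 0.67 = 1,122.4, so 1,123 people. This is 12% above 1000.

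**Step 3: from screened to randomised.** Randomised = screened × share.

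- 1000 × 0.67 = 670.
- Shortfall: 752 − 670 = 82, and 82 / 752 = 10.9%.

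**Step 4: what share would make 1000 right?**

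- 752 / 1000 = 75.2%; equivalently 752 / 0.75 = 1,003.
- The only other cohort percentage in the article is 79% in the Introduction. That describes people sedentary for more than 9.5 hours with minimal moderate-to-vigorous activity, which is not the two-profile rule used for randomisation. It does not support 75%.

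**Step 5: power if recruitment closed at 1000 screened.** Solve the Step 1 formula for the power term at N = 670:

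- z = [√670 × 0.0839 − 1.960 × 0.7659] / 0.7690 = 0.871, so power = 0.81.
- The same at N = 752: z = 1.039, so power = 0.85, as planned.

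**Step 6: the forecast.** The article does not define whether the 2 to 3 included per hospital per month are screened or randomised.

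- If randomised: 20 × 2 × 18 months = 720, and 20 × 3 × 18 = 1,080. The range 720 to 1,080 contains both 752 and 762.
- If screened, over the 18 months of the power calculation: 720 × 0.67 = 482 to 1,080 × 0.67 = 724 randomised. Over the roughly 26 months from November 2023 to December 2025: 1,040 × 0.67 = 697 to 1,560 × 0.67 = 1,045.
- 762 exceeds 752 by 10, or 1.3%.

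**The case against.** The best defence is that 1000 is a loose expectation and not a rule. The Sample size section and the abstract both qualify it with a word of approximation, while 752 randomised is the stated requirement. If 67% turns out to be right, the natural consequence is that the team assesses about 120 more people and still reaches 752. The analysis and the required size are untouched.

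Most of this stands, and it limits the seriousness of the point. It does not remove the error: a 12% gap is more than rounding, the figure is drawn as a conclusion from 67%, and Table 1 gives 1000 without qualification.

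A reader might infer three stronger things that the article does not support.

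- *That the trial will end 82 participants short.* No section stops recruitment at 1000 screened. The loss of power is conditional on someone treating 1000 as the end point. It should also not be combined with any question about how long participants are followed, which is a separate matter.
- *That the forecast of 762 is wrong.* A forecast need not equal a target, and 762 is within 1.3% of 752. The Methods opening uses inclusion for those who are then randomised, and on that reading the 18-month range covers both numbers.
- *That 20 against about 30 hospitals, or 1.5 years of accrual against a window of about 26 months, are contradictions.* Twenty may be a cautious number of active sites. The accrual period is an input to the power calculation, while the calendar window may include start-up. Neither is shown to be an error.

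**Conclusion.** The screening figure is wrong as written. On the article's own numbers, 752 randomised at a 67% share needs about 1,122 screened, while 1000 screened gives 670. The abstract's pairing of about 1000 with 752 implies roughly 75%, which nothing in the article supports.

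The point is of moderate weight. It is an error in a planning figure and does not undermine the design or the 752. The worst consequence, a fall in power from 85% to about 81%, follows only if recruitment closes at 1000 screened, and it assumes the exponential model of Step 1. All the arithmetic assumes that 67% carries over from the cohort to this trial's screened population and that nobody is lost between the baseline visit and randomisation. Any such loss would widen the gap. The forecast and the hospital count need clarifying and are not findings in themselves.

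**What to change.** 1. Restate the expected number screened as about 1,120 to 1,125 in the abstract, Table 1 (with the registry entry) and the Sample size section. Alternatively, keep about 1000 and state and justify an eligible share near 75%, for example from the share observed among participants already screened.
2. State that recruitment ends when 752 participants have been randomised, not when 1000 have been screened.
3. As a minor clarification, say whether 2 to 3 participants per hospital per month are screened or randomised, and reconcile 762 with 752 and 20 hospitals with about 30, or show how each was derived.

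Items 1 and 3 are changes to text and the registry. The real cost is about 120 additional baseline visits (1,122 − 1000) if 67% holds. The randomised target, the design and the analysis stay as they are.

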## Introduction

 Globally, stroke is the greatest contributor to the burden of disease, characterised by a high number of disability-adjusted life years.^1^ The combination of a rising stroke incidence and improvements in acute care has led to a higher number of people living with less residual symptoms after stroke.^2^ However, these people are still at risk of a new major cardiovascular event or death (MACE). A quarter of the people will have a MACE within the first year after stroke.^3^ On top of that, the societal costs incurred by a Dutch stroke patient are high, averaging €29 484 in the first year post stroke.^4^ This stresses the importance of secondary prevention in stroke patients who are at risk for MACE from both the patients’ and societal perspective.

Known risk factors for MACE include an elevated systolic blood pressure, a high body mass index and unhealthy lifestyle factors, such as unhealthy 24-hour movement behaviour (sleep, sedentary behaviour (SB) and physical activity).^5 6^ SB is defined as any waking behaviour with an energy expenditure of ≤1.5 metabolic equivalents, while being in a sitting, lying or reclining posture.^7^ There is increasing evidence that suggests that high levels of SB are strongly adversely associated with cardiometabolic health.^8^ Since the amount of time spent in one behaviour will directly modify the time spent in another, research and interventions should integrate this 24-hour movement behaviour.^9^

Due to its multifactorial nature, changing the 24-hour movement behaviour is a challenging task.^10^ The personal situation, including physical or cognitive capabilities and the (social) environment, varies per individual and therefore requires personalised coaching to enable behavioural change.^10^ Behavioural change is highly needed, since our cohort study showed that 79% of the stroke population was highly sedentary (>9.5 hours) and spent minimal time in moderate to vigorous physical activity (MVPA).^11^ A recent review showed that there are no effective interventions to support community-dwelling stroke patients in reducing SB.^12^ To the best of our knowledge, there are no interventions focusing on specifically targeting the 24-hour movement behaviour in people with stroke.

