The 24-hour movement behaviour consists of sleep quantity, sedentary time, MPVA and LPA. Participants will wear the ActivPAL accelerometer for eight consecutive days during T0, T1, T2 and T4. Daily estimates will be derived from ActivPAL data using the newest R package GGIR.^49^ Within the compositional data analysis (CoDA), SB, MVPA, LPA and sleep quantity are considered as proportions that sum up to 1 (eg, 24 hours).^50^ The raw accelerometry data will be converted into a compositional dataset using the GGIR package. Isometric log-ratios will be used to map the compositional dataset into real-valued coordinates, allowing standard statistical methods to be used. The compositional dataset will be analysed using multivariate analysis of variance (MANOVA) testing overall differences in 24-hour movement patterns between the control and experimental groups. Compositional differences will be calculated via perturbation and visualised using ternary plots.^51^ The usage of CoDa and MANOVA is strongly favoured over traditional analytical techniques when analysing movement behaviours.^52^

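### The 47 per group for sedentary behaviour rests on a pilot group mostly above 9.5 h a day and is not shown to apply to the randomised mix of prolongers and movers (minor; free improvement)

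*Protocol article*

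**What the plan says.** The last paragraph of Sample size in the protocol article says that sedentary behaviour can be studied in fewer people than the primary outcome. Its planning SD comes from the pilot, where "the target group had an average of 11 hours and 21 min of sedentary time per day, with an SD of 77 min/day". The target difference is a cited minimal detectable change of 45 min between groups. At a two-sided 5% level and 80% power, "a sample size of 47 people per group is needed". It then adds: "Accounting for a dropout rate of 20%, 59 participants per group will be used for this analysis".

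Study procedures defines two profiles that enter randomisation: prolongers, at or above 9.5 h of sitting a day, and movers, below 9.5 h. Each has further conditions on bout length or physical activity. Randomisation is done "with stratification according to these two profiles", and Sample size names both profiles as the target population, with 376 per group randomised.

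Statistical analysis describes a MANOVA on log-ratio coordinates, "testing overall differences in 24-hour movement patterns between the control and experimental groups". The outcome table schedules the activity monitor at baseline and at 4, 6 and 12 months, without naming a subset.

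**The concern.** The pilot mean is 681 min a day and the cut-off between the profiles is 570 min. A group with that mean and an SD of 77 min would have few members below the cut-off, yet the trial enrols a whole stratum there. Two planning inputs could therefore be wrong for the randomised population. The SD of sedentary minutes in a mixture of two separated groups exceeds the SD within either one. The average effect could also be smaller than 45 min if people who already sit less reduce their sitting less. Either would leave 47 per group short of 80% power.

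This matters in practice only if the analysis really uses about 59 per group, as the sentence on dropout can be read to say. Interpretation is a separate matter: a single overall contrast by arm does not show whether the two profiles responded alike.

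**Working it through.** **Inputs from the protocol article.** SD 77 min, difference 45 min, two-sided 0.05, power 0.80, dropout 20%, pilot mean 11 h 21 min = 681 min (all Sample size); cut-off 9.5 h = 570 min (Study procedures); 376 randomised per group and 67% of the cohort being prolongers or movers (Sample size); "79% of the stroke population was highly sedentary (>9.5 hours" (Introduction).

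**Inputs not given, assumed here.** Mover mean 8.5 h = 510 min, mover SD 60 min, mover share m from 10% to 31%, and mover effect either 45 min or zero. Prolongers are given the pilot mean and SD.

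**1. The stated figure.** Normal approximation: n = 2 × (1.960 + 0.842)² × 77² / 45² = 46.0. The two-sample t-test version gives 46.9, so 47. Dropout: 47 / 0.80 = 58.75, so 59. Both figures reproduce. The mean of 681 min does not enter the formula.

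**2. Where the pilot group lies.** (570 − 681) / 77 = −1.44. Under normality 7.5% of such a group sits below 9.5 h.

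**3. Largest mover share.** If 79% exceed 9.5 h, at most 21% are below it. If the 67% describes the same cohort (both figures carry the same citation), movers are at most 0.21 / 0.67 = 31% of those randomised. The actual share is not stated.

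**4. SD of the unadjusted mixture.** SD² = (1 − m) × 77² + m × 60² + m(1 − m) × (681 − 510)².
- m = 0.10: 5336 + 360 + 2632 = 8328, SD 91.
- m = 0.20: 4743 + 720 + 4679 = 10142, SD 101.
- m = 0.31: 4091 + 1116 + 6255 = 11462, SD 107.

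Without the last term, which adjustment for profile removes, the SDs at m = 0.10 and 0.31 are 75 and 72.

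**5. Consequences at 47 per group (t-test).** With no response in movers, the average effect is 45 × (1 − m).

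| Scenario | m | Effect (min) | SD (min) | n per group for 80% | Power at 47 |
|---|---|---|---|---|---|
| Both profiles gain 45, unadjusted | 0.10 | 45 | 91 | 66 | 66% |
| | 0.20 | 45 | 101 | 80 | 57% |
| | 0.31 | 45 | 107 | 90 | 52% |
| Movers gain 0, unadjusted | 0.10 | 40.5 | 91 | 81 | 57% |
| | 0.20 | 36 | 101 | 124 | 40% |
| | 0.31 | 31 | 107 | 188 | 29% |
| Movers gain 0, profile adjusted, SD kept at 77 | 0.10 | 40.5 | 77 | 58 | 71% |
| | 0.31 | 31 | 77 | 98 | 49% |
| Both gain 45, profile adjusted, SD kept at 77 | any | 45 | 77 | 47 | 80% |

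Adjustment removes the between-profile spread. It does not remove dilution, if there is any.

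**6. Everyone analysed.** 376 × 0.80 = 300 evaluable per group. In the least favourable row (31 min, SD 107) power is 94%. A harsher variant gives movers an SD of 77 as well, so the pooled SD is 110.6 and the effect 30.9 min. Then 30.9 / (110.6 × √(2/300)) − 1.96 = 1.46, or 93% power. That variant needs 201 per group for 80% power (normal approximation), which is 201 / 376 = 53% of those randomised.

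All of this concerns sedentary minutes, the quantity the article plans on, and not the multivariate test of the composition.

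**The case against.** The strongest reply is that 47 does not size this trial. It supports the remark that fewer people would do, while 376 per group are randomised and the monitor is scheduled without restriction to a subset. With everyone analysed, none of the scenarios above threatens the overall comparison. This stands, and it is why the point is minor.

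Second, the stated outcome is change over time with a baseline measurement. A change score, or adjustment for baseline or profile, would remove much of the gap between profiles that inflates the SD. An article may leave covariates to the analysis plan. This also stands: not naming the profile in the model is no error here, and the larger SD arises only in an unadjusted comparison of levels.

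Third, the pilot's entry criteria are not shown. That its members were mostly above 9.5 h is inferred from a mean and SD under normality, and these figures cannot show bout length or activity, which also define the profiles. This limits the inference but does not remove the lack of support for applying the SD to the mix.

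A reader might go further and infer that the contrast is diluted and that 47 is wrong. The article does not support that. It gives no share, SD or response for movers, and 47 stands if they also gain 45 min and profile is adjusted for. A reader might also conclude that prolongers should be the group for the 45 min target. The article names both profiles as its target population, so that would change the question and not correct the plan.

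**Conclusion.** The 47 and 59 follow exactly from their inputs. They are unsupported for the randomised mix, but not disproved. The shortfall is conditional: at 47 per group, power is about 66% to 52% in an unadjusted comparison with a full effect in both profiles, and 57% to 29% if movers do not respond. These ranges rest on the assumed mover mean, SD and share, and the 31% upper share rests on reading the 79% and 67% as one cohort.

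The shortfall matters only if the 59 per group is meant literally as the analysis set. With about 300 evaluable per group, power for sedentary minutes is at least about 93% throughout, so the overall test is not underpowered. What remains is an ambiguous sentence about who is analysed, an unqualified planning figure, and a stratification factor that could improve the analysis at no cost in data. Severity is minor, and the change is a free improvement.

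**What to change.** 1. In the movement-behaviour model under Statistical analysis, include the randomisation profile and preferably the baseline composition. Keep the overall arm effect as the main contrast, and report profile-specific estimates as supportive.
2. In Sample size, replace the sentence on 59 per group with a statement that all randomised participants with valid monitor data are analysed, and that the smaller number only shows that this outcome needs fewer people.
3. Either say that 47 and 59 rest on a pilot group mostly above 9.5 h, or restate them for the mix with an explicit mover share, SD and effect, and say whether profile is adjusted for.

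The cost is wording. Profile is already recorded as the stratification factor and the monitor data are already scheduled. The downside is that estimates in the smaller profile will be imprecise, so they should be read with their intervals and not as separate tests.
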